## Abstract

**Background:**

Ankle sprains are the most common sports and physical activity related injury. There is extensive evidence that there is a twofold increased risk for injury recurrence for at least one year post injury. In up to 50% of all cases recurrences result in disability and lead to chronic pain or instability, requiring prolonged medical care. Therefore ankle sprain recurrence prevention in athletes is essential. This RCT evaluates the effect of the combined use of braces and neuromuscular training (e.g. proprioceptive training/sensorimotor training/balance training) against the individual use of either braces or neuromuscular training alone on ankle sprain recurrences, when applied to individual athletes after usual care.

**Methods/Design:**

This study was designed as three way randomized controlled trial with one year follow-up. Healthy individuals between 12 and 70 years of age, who were actively participating in sports and who had sustained a lateral ankle sprain in the two months prior to inclusion, were eligible for inclusion. After subjects had finished ankle sprain treatment by means of usual care, they were randomised to any of the three study groups. Subjects in group 1 received an eight week neuromuscular training program, subjects in group 2 received a sports brace to be worn during all sports activities for the duration of one year, and group 3 received a combination of the neuromuscular training program and a sports brace to be worn during all sports activities for the duration of eight weeks. Outcomes were assessed at baseline and every month for 12 months therafter. The primary outcome measure was incidence of ankle sprain recurrences. Secondary outcome measures included the direct and indirect costs of recurrent injury, the severity of recurrent injury, and the residual complaints during and after the intervention.

**Discussion:**

The ABrCt is the first randomized controlled trial to directly compare the secondary preventive effect of the combined use of braces and neuromuscular training, against the use of either braces or neuromuscular training as separate secondary preventive measures. This study expects to identify the most effective and cost-efficient secondary preventive measure for ankle sprains. The study results could lead to changes in the clinical guidelines on the prevention of ankle sprains, and they will become available in 2012.

**Trial registration:**

Netherlands Trial Register (NTR): NTR2157

## Background

The burden of ankle sprains in sports is high. Ankle sprains are the most common sports and physical activity (PA) related injury [1-4]. It has been estimated that about 25% of all injuries across all sports are ankle injuries. Of all ankle injuries, about 85% are acute lateral ankle sprains. As an example, in the Netherlands the most recent count of sports injuries showed that there is an estimated absolute number of 3, 5 million acute sports injuries each year in a sporting population of 11 million participants [4]. Of these a total of 600,000 are to the ankle, making the estimated annual number of sports related ankle sprains 510,000, of which half is (para-)medically treated. A recent Dutch study [5] showed that, disregarding the requirement of medical treatment, the mean total (direct and indirect) cost of one ankle sprain is approximately €360. This would give a rough estimate of the annual sports related ankle sprain costs being €184 million.

In addition to the sheer magnitude of the ankle sprain 'problem' in sports, there is extensive evidence that there is a twofold increased risk for injury recurrence for at least one year post injury [6-9]. In up to 50% of all cases recurrences result in disability and lead to chronic pain or instability, requiring prolonged medical care [10]. This increased ankle sprain recurrence risk has been found to exist even after completion of medical treatment [9,11,12]. Therefore, the advocation of braces and neuromuscular training (synonymous: proprioceptive training/sensorimotor training/balance training) after usual care is a justified part of treatment, and has a significant and important impact on a patient's current and future health, as well as future sports and physical activity participation.

A recent systematic review revealed that both braces as well as neuromuscular training have been proven equally effective for the secondary prevention of ankle sprains [13]. Both account for an approximated 50% overall reduction in recurrent ankle sprain rate. In contrast, individuals with no history of ankle sprains do not seem to benefit from these preventive measures. Hence, it can be concluded from the current literature that despite different preventive pathways taping, bracing and neuromuscular training are separately linked to a similar secondary preventive effect [13]. Based on these outcomes, in theory, a combination of an external prophylactic measure (tape or brace) with neuromuscular training is argued to achieve the best preventive outcomes with minimal burden for the athlete.

Therefore, the current three-way randomised controlled trial evaluates the (cost-) effectiveness of the combined use of braces and neuromuscular training against the individual use of either braces or neuromuscular training alone.

## Methods/Design

The CONSORT statement was followed to describe the design of this study [14]. This statement is a checklist intended to improve the quality of reports of randomized controlled trials.

### Study outline

The Ankles Back in randomised Controlled trial (ABrCt) is a three way randomized controlled trial with one year follow-up. The study design and flow of the participants are shown in Figure 1.

**Figure 1 F1:**
[figure not shown]
**Study design ABrCt and flow of the participants**.

The study is funded by the Netherlands Organization for Health Research and Development (ZonMW). The study design, procedures and informed consent procedure were approved by the Medical Ethics Committee (number 31785.029.10) of the VU University Medical Centre, the Netherlands. Trial register number NTR 2157. All participants provided written informed consent.

### Hypotheses

The first hypothesis of this study is that each of the three interventions will lead to a 50% reduction of ankle sprain recurrence incidence. The second hypothesis is that there will be a difference in costs-effectiveness of the three interventions. The third hypothesis is that there will be differences in ankle sprain related complaints (e.g. chronic instability, pain, feeling of giving way) between the three interventions.

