### Sample size

As there is no scientific evidence on the combined effect of braces and neuromuscular training it is assumed that the effectiveness is comparable to the separate effect of braces or neuromuscular training alone[13]. Therefore, while reliable effect-sizes to calculate power are missing, a power analysis was done from the view of the intervention costs.

A recent Dutch study on ankle sprains and their prevention collected direct and indirect cost data related to ankle sprains [5]. Within this data a subgroup analyses of previously injured athletes revealed that the mean costs of a recurrent ankle sprain are €27 with an SD of €108. Home based neuromuscular training program costs are estimated at €25. Sports braces costs are estimated at €50. Consequently usual care costs are about €75 per recurrent ankle sprain. Based on an expected difference of €50 in costs (i.e, the cost difference between usual care and a neuromuscular training program), a total of 99 participants per group is needed. Taken into account an attrition rate of 20% this means that a total sample of 356 participants is required at baseline.

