### Recruitment of study population

Participants were recruited through the internet. Information on the study and a call for participation were available on the website: http://www.anklesbackincontrol.nl. The study was supported by the Dutch Association for Sports and Exercise Medicine (VSG), the Royal Dutch Physiotherapy Association (KNGF), the Dutch Orthopedic Association (NOV) and the Dutch College of General Practitioners (NHG). The participating organizations placed a hyperlink on their website. Hereby, individuals seeking medical information regarding ankle sprains in any of these sites came across this call for participants. Similar calls were placed on the websites of sporting associations of sports with a relatively high ankle sprain rate (e.g. soccer, volleyball, handball, basketball, korfball and tennis). Where possible existing electronic newsletters of sporting associations were used to contact potential participants directly. Next to the mentioned calls for participation on websites, we recruited actively by placing calls for participation on sports-related internet fora, as well as by electronic newsletters. This method of recruitment resulted in a sample of participants from a wide spectrum of different activities, sports and ages. Thus we created a sample representative to the Dutch sporting population. A similar recruitment strategy was successfully employed in a previous study on the same topic [15].

Recruitment of participants for the ABrCt study took place between April 2010 and May 2011. A total of 450 people were interested to participate in the ABrCt study and reacted on the call for subjects with a recent ankle sprain. A total of 18 athletes were classified as non-responders after a maximum of ten attempts to contact them through telephone or email failed. Of 432 people who were available for inclusion, 48 were excluded. Reasons for exclusion were: no return of baseline questionnaire (3), still undergoing treatment at the end of the inclusion period (5), no agreement on informed consent (2), vestibular complaints (2), non-recent ankle sprain (injury > 2 months before inclusion) (25), other serious injury (e.g. fracture of the ankle) (5) and private reasons (6). After completion of the baseline questionnaire and informed consent, 384 athletes were randomly assigned to the neuromuscular training group (n = 122), brace group (n = 126), and combined group (n = 136).

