### Statistical analyses

To evaluate the success of the randomisation, baseline values were analysed for differences between intervention group and control group, using a chi-square for categorical data and a student's t-test for numerical data.

All analyses were carried out according to the intention-to-treat principle. Cox-regression analysis was used to compare ankle recurrence risk between the intervention groups, using a significance level of P < 0.05. Other variables were checked for confounding and/or effect-modification and were adjusted for accordingly. Absence from sports was tested between groups using a Mann-Whitney test, since absence from sports due to an injury is not normally distributed [11].

Mean direct, indirect and total costs were estimated and compared between the three groups, both for the costs per subject in the injured population and for the costs per subject in the total population. Because costs are not normally distributed, 95% confidence intervals for the differences in mean costs were obtained by bias corrected and accelerated bootstrapping (2000 replications) [21]. Differences in costs and differences in ankle sprain recurrences were compared against the cheapest intervention (neuromuscular training) in a cost-effectiveness ratio, which estimated for each other condition the additional cost to prevent one ankle sprain recurrence. Confidence intervals for the cost-effectiveness ratio were calculated with bootstrapping, using the bias-corrected percentile method with 5000 replications. Uncertainty regarding the estimate of this ratio was expressed on a cost-effectiveness plane.

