### Impact of results

This study expects to identify the most effective and cost-efficient secondary preventive measure for ankle sprains. The study results could lead to changes in the clinical guidelines on the prevention of ankle sprains, and they will become available in 2012.

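### Hypothesis 1 predicts that each intervention halves recurrence, but all three arms are active and no reference rate exists, so the trial can neither estimate nor test it

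*Protocol article*

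**What the plan says.** The Hypotheses section opens with the statement that "each of the three interventions will lead to a 50% reduction of ankle sprain recurrence incidence". It does not say against what. The other two hypotheses, on cost-effectiveness and residual complaints, are comparisons between the three interventions.

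The Background gives the aim as a trial that "evaluates the (cost-) effectiveness of the combined use of braces and neuromuscular training against the individual use of either braces or neuromuscular training alone". The Interventions section confirms that all three arms are active: training for eight weeks, a brace for a year, or both for eight weeks. Usual care precedes randomisation in every arm and is not itself an arm.

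For the primary outcome, Statistical analyses says: "Cox-regression analysis was used to compare ankle recurrence risk between the intervention groups, using a significance level of P < 0.05". It gives no equivalence or non-inferiority margin and no external or historical comparison.

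Under Sample size, the effect of the combination is not known, so "it is assumed that the effectiveness is comparable to the separate effect of braces or neuromuscular training alone". The trial is sized on money: "while reliable effect-sizes to calculate power are missing, a power analysis was done from the view of the intervention costs".

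Other places also presuppose a control that the design lacks. Statistical analyses compares baseline values between an intervention group and a control group, using a t-test for numerical data, and names a Mann-Whitney test for absence from sports. Sample size uses the cost difference between usual care and training. The Co-intervention part of the Discussion describes the aim as added value over usual care.

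**The concern.** A percentage reduction needs a reference. Here neither the design nor the cited figures supply one, so the leading hypothesis for the primary outcome will have no result. This is not a detail that a fuller analysis plan could fill in, because the randomised data needed for it are not collected.

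The plan also makes a null finding likely. Both the first hypothesis and the sizing assumption imply little or no difference between arms. A non-significant Cox comparison would be compatible with all three interventions halving recurrence, with none of them working, and with too few events to tell. Since the article expects its results to bear on clinical guidelines, it matters which of these may be claimed.

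**Working it through.** **1. Is there any reference for the 50%?**

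- Randomised arms: training, brace, combination. None is usual care alone.
- Reference rate: the primary outcome is recurrences per 1,000 hours of sport, and the article gives no such rate for untreated athletes. The Background gives only relative figures: a twofold increased risk after a sprain, and about 50% reduction for each measure in a cited review.
- Athletes' own history: the baseline questionnaire records past injuries, but everyone entered because of a recent sprain, and no before-after comparison is planned.

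**2. What can the three arms identify?**

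Let λ0 be the recurrence rate under usual care alone and r the rate ratio of each arm against it. The arm rates are r_T·λ0, r_B·λ0 and r_C·λ0. Any between-arm ratio is, for example, (r_C·λ0)/(r_T·λ0) = r_C/r_T, so λ0 cancels.

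- All r = 0.5 (hypothesis 1 true): every ratio is 0.5/0.5 = 1.
- All r = 1 (no arm works): every ratio is 1/1 = 1.

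The Cox comparison cannot separate these two states, and both are its null hypothesis.

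**3. The plan's own size.**

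Inputs from Sample size: difference €50, SD €108, attrition 20%. Two-sided 5% and 90% power are my assumptions; the article states neither the sidedness nor the power.

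n per group = 2·(1.960 + 1.282)²·108²/50² = 2 × 10.51 × 4.666 = 98.1, rounded up to 99. Total = 3 × 99 × 1.2 = 356.4, which matches the stated 356.

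The figures reproduce, but they rest on cost and on a contrast with usual care. They say nothing about precision for recurrence.

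**4. How precise would a null result be?**

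Per arm: 356/3 ≈ 119. One-year recurrence is not given, so I assume 10% to 30%. Events per pair = 2 × 119 × risk. The 95% CI for an observed hazard ratio of 1 is exp(±1.96 × 2/√events).

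| Assumed risk | Events per pair | Half-width, log HR | 95% CI |
|---|---|---|---|
| 10% | 23.8 | 3.92/4.88 = 0.80 | 0.45 to 2.23 |
| 30% | 71.4 | 3.92/8.45 = 0.46 | 0.63 to 1.59 |

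With the 99 per group of the sample-size calculation, the intervals widen to 0.41 to 2.41 and 0.60 to 1.66.

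**5. Could equality be shown?**

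The article gives no margin. With an assumed hazard-ratio margin of 1.5, two one-sided 5% tests, 80% power and a true ratio of 1, events per pair = 4·(1.645 + 1.282)²/(ln 1.5)², about 209. That compares with the 23.8 to 71.4 expected above.

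**The case against.** The best defence is that the between-arm aim is stated clearly in the Background and that hypotheses 2 and 3 are already between-arm. On this reading the fault is one sentence that presents an expectation from earlier evidence as a trial hypothesis. That is fair, and it is why the remedy is mainly rewording. It does not rescue the sentence, which is the first hypothesis and concerns the primary outcome. The intervals in step 4 do rest on assumed recurrence, but the untestability needs no figure.

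Four stronger readings are tempting, and the documents do not support them.

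- **That missing multiplicity control prevents naming a best arm.** Three unadjusted pairwise tests at 5% do give a 12.2% chance of at least one false difference when all arms are equal (simulated). Naming a best arm, however, requires it to beat both others. The chance of doing so falsely is 1.4% when all three arms are equal and at most about 5.0%, when two tie for best. The article also does not say that the Cox comparison is three pairwise tests, and silence on multiplicity may be left to a fuller plan. The expectation that "This study expects to identify the most effective and cost-efficient secondary preventive measure for ankle sprains" also rests partly on the planned cost-effectiveness estimates.
- **That the real obstacle to a best arm has been dealt with.** It has not: that obstacle is low power. With 99 per arm and 10% to 30% risk in the worse arm, power for a between-arm hazard ratio of 0.5 is about 27% to 65%.
- **That the trial plans to conclude equal effectiveness.** That description belongs to the cited review. Hypothesis 1 implies equality, but no passage says a non-significant result will be read that way.
- **That the Background contradicts the sample-size assumption.** The Background says only that a combination "with neuromuscular training is argued to achieve the best preventive outcomes with minimal burden for the athlete", as theory. A motivating theory and a sizing assumption made for lack of data can coexist.

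**Conclusion.** The point holds for hypothesis 1. As written it cannot be estimated or tested, because all three arms are active and the article has no reference rate or external comparison. This follows from the design and needs no assumption. If the hypothesis were true, the planned Cox test would be under its null, so non-significance could not confirm it.

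The size depends on assumed one-year recurrence of 10% to 30% and 119 per arm without losses. At the low end, an observed hazard ratio of 1 would exclude neither a halving nor a doubling between arms; at the high end it would still not exclude a 1.5-fold difference. The between-arm aim is unaffected, and a finding that one arm beats both others would remain valid.

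**What to change.** 1. Restate hypothesis 1 as between-arm contrasts: combined versus training, combined versus brace, and brace versus training. Report each as a hazard ratio with its 95% confidence interval.
2. Move the 50% to the rationale and label it as an expectation from earlier studies.
3. State that no reduction against usual care or no intervention will be claimed, and align the added-value sentence under Co-intervention with this.
4. State that comparable effectiveness will be claimed only if the confidence interval lies within a margin fixed before analysis.
5. In Statistical analyses, replace the intervention-versus-control wording with the three arms. Say how the t-test and the Mann-Whitney test, both two-group methods, are applied to three arms, or name three-group methods instead.

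This costs rewording only; no data collection changes. The downside is that an equality claim will probably not be reachable at this size, so a null result would have to be reported as inconclusive.

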### Participants

Healthy participants between 18 and 70 years of age, who are actively participating in sports and who have sustained a lateral ankle sprain up to two months prior to inclusion, were eligible for inclusion in the study. All primary treatment options were allowed, i.e. no treatment, self treatment or (para-)medical treatment. Responders were excluded if they did not master the Dutch language, had a history of vestibular complaints, or had a different injury than a lateral ankle sprain in the same ankle (e.g. fracture of the ankle). This resulted in a diverse source population of athletes from all types and levels of sports participating in the study. The interventions were considered to be appropriate for all athletes. Hupperets et al found no side effects of the neuromuscular training program [15]. Other studies reported changed biomechanics, in the use of braces as a secondary preventive measures, but no other side effects were reported [16].

### Sample size

As there is no scientific evidence on the combined effect of braces and neuromuscular training it is assumed that the effectiveness is comparable to the separate effect of braces or neuromuscular training alone[13]. Therefore, while reliable effect-sizes to calculate power are missing, a power analysis was done from the view of the intervention costs.

A recent Dutch study on ankle sprains and their prevention collected direct and indirect cost data related to ankle sprains [5]. Within this data a subgroup analyses of previously injured athletes revealed that the mean costs of a recurrent ankle sprain are €27 with an SD of €108. Home based neuromuscular training program costs are estimated at €25. Sports braces costs are estimated at €50. Consequently usual care costs are about €75 per recurrent ankle sprain. Based on an expected difference of €50 in costs (i.e, the cost difference between usual care and a neuromuscular training program), a total of 99 participants per group is needed. Taken into account an attrition rate of 20% this means that a total sample of 356 participants is required at baseline.

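### The sample size takes its cost inputs per recurrent sprain but counts its result in participants, and its €27 conflicts with the roughly €360 per sprain in the Background

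*Protocol article*

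**What the plan says.** The Sample size section of the protocol article says that reliable effect sizes are lacking and bases the power analysis on costs. Its inputs are:

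- From a subgroup of previously injured athletes in an earlier Dutch study, "the mean costs of a recurrent ankle sprain are €27 with an SD of €108".
- "Home based neuromuscular training program costs are estimated at €25", and braces at €50.
- "Consequently usual care costs are about €75 per recurrent ankle sprain".
- An expected difference of €50, described as usual care against the training programme, that is €75 − €25.

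The result is that "a total of 99 participants per group is needed", then "Taken into account an attrition rate of 20% this means that a total sample of 356 participants is required at baseline".

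Two other places bear on the unit. The Background cites the same earlier study for the statement that "the mean total (direct and indirect) cost of one ankle sprain is approximately €360". The Statistical analyses section plans cost comparisons "both for the costs per subject in the injured population and for the costs per subject in the total population". Under Injury registration, cost diaries go only to participants who sustain a sprain.

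**The concern.** A cost per recurrent sprain exists only for a participant who re-sprains. If the SD of €108 and the usual-care cost of €75 are on that unit, the formula returns the number of recurrent sprains to be costed in each group, and it can be read as participants only if essentially everyone re-sprains. The paragraph does read it as participants and gives no recurrence proportion.

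The unit is also doubtful in itself. A mean of €27 for one recurrent sprain sits badly beside about €360 for one sprain from the same source, and nothing in the text explains the gap. A mean of €27 with an SD four times as large is what one would expect of a cost per athlete in which most athletes cost nothing.

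This is the trial's only justification of its size. As written, a reader cannot tell which of the two planned cost comparisons it supports.

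**Working it through.** **Inputs from the article.** Difference €50; SD €108; 99 per group; about €360 per sprain (Background). The €27 mean does not enter the sample-size formula.

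**Inputs assumed.** Two-sided alpha 5% (the article gives P < 0.05 for the Cox analysis only), and a recurrence proportion p over follow-up, with one costed recurrence per injured participant. The article gives no absolute recurrence proportion, so p is shown as a range.

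**1. Reproducing 99.** n per group = 2 × (1.960 + 1.282)² × 108² / 50² = 98.05, rounded up to 99. The t-test version gives 99.02, and power at 99 is 90.0%. The implied target is therefore 90%. At 80% power the formula gives 74. At 80% power with alpha 0.05/3 it gives 98, which is close but not the stated figure.

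**2. The unit as written, among the injured.** Cost observations per group = 99p, with SD €108 and difference €50.

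**3. The unit as written, per participant.** If €50 is a difference per recurrent sprain, the difference per participant is 50p. The per-participant SD is √[p × (108² + 27²) − (27p)²]. For p = 20%: √[0.2 × 12,393 − 5.4²] = √2,449 = €49.5, against a difference of €10.

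| p (assumed) | injured per group | power for €50 among injured | difference per participant | SD per participant | power per participant, n = 99 |
|---|---|---|---|---|---|
| 10% | 9.9 | 16% | €5 | €35 | 17% |
| 20% | 19.8 | 30% | €10 | €50 | 29% |
| 30% | 29.7 | 42% | €15 | €60 | 41% |
| 50% | 49.5 | 63% | €25 | €78 | 62% |
| 95% | 94 | 88% | €47.50 | €105 | 88% |
| 100% | 99 | 90% | €50 | €108 | 90% |

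The two routes agree, and 90% is approached only when nearly everyone re-sprains. Obtaining 99 recurrent sprains per group would take 99/p completers: 990, 495, 330 or 198 at p = 10%, 20%, 30% or 50%.

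**4. The alternative unit, per previously injured athlete.** 360/27 = 13.3, and 27/360 = 7.5%. If 7.5% of athletes have a sprain costing a fixed €360 and the rest cost nothing, the mean is €27 and the SD is 360 × √(0.075 × 0.925) = €95. Some spread between sprain costs would raise this towards €108. The pair €27 and €108 is thus broadly what a per-athlete cost with many zeros looks like. On this reading 99 participants per group give 90% for a €50 difference in mean cost per participant, and the per-sprain labels on €27 and €75 are wrong. The injured-population comparison would then rest on about 99 × 0.075 = 7 participants per group.

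**The case against.** The strongest reply is that the section never claims power for cost per recurrent sprain. It sizes the trial from intervention costs, which fall on every allocated participant, and it counts participants. This points to cost per participant in the total population, where the per-athlete reading makes 99 adequate. That reply largely stands. The per-athlete reading is the likelier one, and the article promises no power for the injured-population comparison, so low numbers there break no stated claim.

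A second reply is that even on the written unit the per-participant SD is only €35 to €78 for p from 10% to 50%, so a €50 difference would be detected with more than 99% power. This does not stand. It keeps the full €50 for every participant although the €75 behind it is stated per recurrent sprain. Scaling the difference by p, as in step 3, removes the gain.

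Two stronger readings should be resisted:

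- A reader might infer that the total-population comparison is also too small, because €360 per sprain and p above 10% imply a per-participant SD above €108: 360 × √(p(1 − p)) gives at least €144 at p = 20%. That combines an assumed recurrence with a cost for ankle sprains in general, not for the previously injured subgroup. The documents do not establish it.
- A reader might infer that the SD fits neither planned cost analysis. It fits one on each reading; the text leaves open which.

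**Conclusion.** The point holds as an inconsistency in the stated basis of the sample size. Three figures (€27, €108, €75) are labelled per recurrent sprain, the result is read as participants, and €27 disagrees about 13-fold with the Background figure from the same source.

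The consequence depends on which label is right. If the written unit is right, 99 participants per group fall well short of the implied 90%: about 16% to 63% among the injured for an assumed recurrence of 10% to 50%, and about 17% to 62% per participant. If the figures are per previously injured athlete, which is likelier, 99 per group stands for total-population cost per participant and the error is one of wording. On neither reading does the size cover the injured-population cost comparison, unless nearly everyone re-sprains.

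The 90% target is inferred from an exact match, not printed, and every power figure below it rests on an assumed recurrence proportion. The article does not show that the trial as a whole is too small for its cost comparison.

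**What to change.** Go back to the source subgroup and establish the unit of €27, €108 and €75. Restate them on that unit and explain how they relate to the roughly €360 per sprain in the Background.

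- If they are per previously injured athlete, remove the per-sprain wording from both sentences and state that 99 per group refers to mean cost per participant in the total population.
- If they really are per recurrent sprain, state that 99 is a number of recurrences per group, give the recurrence proportion assumed, and restate the power for the 356 included with the per-participant difference and SD of step 3.

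In either case print the alpha and power used, and say that the size does not cover the cost comparison in the injured population.

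The cost is a reworded paragraph, a check of the cited source and at most one recalculation. No further enrolment is needed. The price is that the stated precision may look less favourable.
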